#### DNA testing

DNA will be extracted and analysed for the three known NOD2 susceptibility mutations: R702W, G908R and 1007fs by allele-specific PCR amplification [19]. Assays are to be validated by the inclusion of individuals with known NOD2 genotypes derived by DNA sequencing in each genotyping experiment. A greater than 95% success rate is expected for the extraction and amplification of DNA. In the event that DNA is not collected or the PCR procedure fails, the participant will be asked to provide a further sample. While the prevalence of NOD2 mutations is lower or zero in populations not of European ancestry, the penetrance of the gene is not known to vary by ethnicity.

### Outcomes

#### Primary outcome

The primary outcome, assessed six months after the intervention, is making one or more quit attempts of 24 hours or longer in the six months following assessment of CD risk. This end point is a reliable predictor of eventual cessation [20].

#### Secondary cessation outcomes

##### Seven-day smoking cessation at one week

Self-reported smoking cessation will be assessed at one week following receipt of the CD risk assessment.

##### Seven-day smoking cessation at six months

At six months abstinence from smoking in the preceding seven days will be assessed using the Russell standard procedures [21], counting participants lost to follow up as being smokers, and self-reported smoking status will be verified biochemically. Validated abstinence requires smoking no more than 5 cigarettes in the prior seven-day period and a cotinine level of <15 ng/ml.

##### Additional outcomes

Questionnaires administered within telephone calls 1,3 and 4 will assess key variables derived from three psychological theories, specifically Leventhal's self-regulation model of health and illness [22], Protection Motivation Theory [23], and the Theory of Planned Behaviour [24]. We will also assess self-reported smoking-related behaviours (such as use of NRT) and participants' recall and comprehension of their risk assessment.

### Sample size

#### (a) Hypothesis I

The initial sample size estimate comprised 540 smokers who were FDRs of probands with Crohn's disease. 270 would be cluster randomised by family to DNA testing and 270 to the non-DNA arm. Allowing for 20% dropout we expected to follow-up 215 per arm. With this sample size, and allowing for clustering, there was 80% power to detect an odds ratio (OR) of 1.75 for likelihood of engaging in a quit attempt between randomised arms using a two-sided test at the 5% level of significance. In a general population sample without presentation of risk information 29% reported a quit attempt by six-month recall [25]. On this basis we have estimated that the proportion reporting having made one or more quit attempts of 24 hours or more in the preceding six months would be 35% in the non-DNA arm, enabling detection of 49% or higher in the DNA testing intervention arm (OR = 1.75). In order to allow for clustering effects by family the sample size was increased by a design effect of 8%. This was based on a mean cluster size of 1.13 from the pilot study [18] and an allowance that the intracluster correlation (ICC) could be as high as 0.6 based on observing a range of ICCs between 0.3 and 0.87 for behavioural outcomes clustered at the household level [26].

To check the assumptions underlying the sample size calculation, an interim analysis including the first 266 (50%) participants was conducted. This revealed a higher completion rate (87%), confirmed the cluster size (mean cluster size 1.14) and identified the ICC to be zero. The trial steering committee supported a revised sample size calculation based on a follow-up rate of 85% and without the need to account for clustering in the analysis. This meant that without loss of power for primary or secondary outcomes we could follow up 200 per arm, requiring recruitment of only 470 randomised participants.

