**Methods/design:**

A parallel groups randomised controlled trial in which smokers who are FDRs of probands with CD are randomly allocated in families to undergo one of two types of assessment of risk for developing CD based on either:

i. DNA analysis, family history of CD and smoking status, or

ii. Family history of CD and smoking status

The primary outcome is stopping smoking for 24 hours or longer in the six months following provision of risk information. The secondary outcomes are seven-day smoking abstinence at one week and six month follow-ups. Randomisation of 470 smoking FDRs of CD probands, with 400 followed up (85%), provides 80% power to detect a difference in the primary outcome of 14% between randomised arms, at the 5% significance level.

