#### (b) Method

Each participant will be cluster randomised by family to one of the two arms, with allocation on a 1:1 basis. The allocation method will be blocked randomisation with the randomisation sequence prepared by the trial statistician.

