### Statistical analysis

The analysis of the primary outcome, the proportion of participants reporting having made one or more quit attempts of 24 hours or more in the preceding six months, and the secondary cessation outcomes will be compared between arms by estimating a difference in proportions between arms together with a 95% confidence interval, and the p-value from the associated chi-squared test. The odds ratio and 95% confidence interval will also be reported. Analyses will be on an intention to treat basis with the common assumption for secondary cessation outcomes that all participants are classified as smokers except for those biochemically verified as non-smokers. However, for the primary outcome, those missing this outcome will primarily be treated as missing from the analysis. Missing status will be compared between groups, and the primary difference in proportions will be re-assessed assuming that missing data is imputed as no quit attempt. All tests will be two-sided and assessed at the 5% significance level. Sensitivity analyses will be performed to confirm that clustering makes negligible difference to results and no difference to conclusions or interpretations, using Donner's Method [27]. Hypotheses II and III will be assessed by comparing the primary outcome between mutation status subgroups of the DNA arm with each other and with the control arm. To strengthen the interpretation of these non-randomised comparisons, sensitivity analysis will be undertaken to vary the degree to which mutation status may predict outcome, detailed as part of the statistical analysis plan to be prepared prior to analysis.

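### Families are randomised, but the primary test and the revised sample size ignore clustering on the strength of an imprecise interim ICC of zero; the effect is modest and easily repaired

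*Protocol article*

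**What the plan says.** The Randomisation section, part (b) Method, states "Each participant will be cluster randomised by family to one of the two arms, with allocation on a 1:1 basis". The Trial design section also calls the study a cluster randomised trial.

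The Sample size section, part (a) Hypothesis I, gives two calculations. The initial one allowed for families with a mean size of 1.13 and an ICC of up to 0.6, chosen from a cited household range of 0.3 to 0.87. An interim check on the first 266 participants then found 87% completion. It "confirmed the cluster size (mean cluster size 1.14) and identified the ICC to be zero". No interval for the ICC and no count of multi-member families is given. On this basis, and with the steering committee's agreement, the plan moved to "a revised sample size calculation based on a follow-up rate of 85% and without the need to account for clustering in the analysis", and the target fell from 540 to 470 randomised (200 per arm followed up), with the protocol asserting that no power was lost.

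The Statistical analysis section makes the difference in proportions, its 95% confidence interval and a chi-squared test the main analysis, without adjustment for family. Clustering appears once, as a planned check by Donner's Method: "Sensitivity analyses will be performed to confirm that clustering makes negligible difference to results and no difference to conclusions or interpretations".

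**The concern.** An ordinary chi-squared test treats participants as independent. When families are the unit of allocation and relatives behave alike, its p-value is too small and its confidence interval too narrow. Smoking within a family is an outcome for which similarity is plausible, and the protocol's own cited range for household behaviours starts at 0.3.

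The protocol sets this aside because of a point estimate of zero. Only families with two or more participants carry information on the ICC, and at a mean size of 1.14 there are few of them. If the estimate is imprecise, it cannot carry either the choice of an unadjusted primary analysis or the statement that the smaller sample costs no power. The one analysis that respects the unit of randomisation is placed second and worded as though its result were already known.

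**Working it through.** **Inputs from the protocol.** Two-sided 5% level; 35% v 49%; 200 per arm followed up; 85% follow-up (all current plan). Interim: 266 participants, mean family size 1.14, 87% completion, ICC estimate 0. Assumption, not stated in the protocol: every multi-member family is a pair.

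**1. Reproducing the plan's figure.** The pooled two-proportion formula without continuity correction gives 194 per arm for 80% power, against 200 stated. With 200 per arm, power is 81.2%. Recruitment: 2 × 200 / 0.85 = 471, against 470. So the stated sample size reproduces when the ICC is 0.

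**2. Information behind the interim ICC.**
- Families: 266 / 1.14 = 233.
- Extra members: 266 − 233 = 33, so about 33 pairs.
- Pairs with both members followed up: 33 × 0.87² = 25.

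If the extra members were all in families of three, there would be only about 16 such families.

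**3. Precision of an estimate of zero.** For n pairs, an approximate 95% upper limit by Fisher's z is tanh(1.96 / √(n − 1.5)).
- n = 33: tanh(1.96 / √31.5) = 0.34.
- n = 25: tanh(1.96 / √23.5) = 0.38.

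A simulation of the ANOVA estimator (binary outcome, assumed 42% event rate, 25 to 33 pairs plus singletons, 20,000 runs per setting) gives a standard deviation of about 0.18 to 0.20 for the estimate. The chance of an estimate at or below zero is:

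| True ICC | Chance of estimate ≤ 0 |
|---|---|
| 0.2 | 12% to 16% |
| 0.3 | 4% to 6% |
| 0.6 | about 0.1% or less |

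The interim data argue strongly against 0.6, do not clearly exclude 0.3, and do not establish zero.

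**4. Effect on the primary comparison.** With unequal family sizes the design effect is DE = 1 + (Σm²/Σm − 1) × ICC. For singletons and pairs with mean 1.14, Σm²/Σm = (233 − 33 + 4 × 33) / 266 = 1.246 (unrounded counts). The confidence interval is too narrow by 1 − 1/√DE. The real error rate is 2(1 − Φ(1.96/√DE)). Power uses 200/DE per arm.

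| ICC | DE | CI too narrow by | Real alpha | Effective n per arm | Power |
|---|---|---|---|---|---|
| 0 | 1.000 | 0 | 5.0% | 200 | 81.2% |
| 0.2 | 1.049 | 2.4% | 5.6% | 191 | 79.3% |
| 0.3 | 1.074 | 3.5% | 5.9% | 186 | 78.4% |
| 0.34 | 1.084 | 3.9% | 6.0% | 185 | 78.0% |
| 0.38 | 1.093 | 4.4% | 6.1% | 183 | 77.7% |

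Using the mean size in place of Σm²/Σm gives a smaller effect: at ICC 0.3, DE = 1 + 0.14 × 0.3 = 1.042 and power 79.6%.

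**The case against.** The best defence is that families are so small that clustering hardly matters, and that the protocol already commits to Donner's Method, so readers will see an adjusted result. Both points stand. Only a p-value close to 0.05 could change sides. What remains is that the main interval and p-value do not respect the unit of randomisation, and that the check is worded as a confirmation. A rule for what happens if the two analyses disagree may be in the analysis plan, which is not shown, so its absence from the article is not held against it.

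A second defence is that a true ICC of 0.3 would give an estimate at or below zero only 4% to 6% of the time. A one-sided 95% limit by the same formula is 0.28 (33 pairs) to 0.33 (25 pairs). That is fair: 0.3 is at the edge of what the interim data allow, not comfortably inside it.

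Four stronger readings are tempting and are not supported:
- *The trial is seriously underpowered, as at the planning ICC of 0.6.* The interim result makes 0.6 very unlikely, so figures at that value do not describe the current plan.
- *The whole cut from 540 to 470 rests on the zero ICC.* Better follow-up alone takes 540 to about 506 (2 × 215 / 0.85), roughly half of the reduction.
- *The original allowance was too small, so the current target is wrong.* The protocol says "the sample size was increased by a design effect of 8"%, which uses the mean family size and is low if sizes are unequal. But that allowance belongs to the superseded calculation and does not enter the 470.
- *The comparisons by mutation status have the same fault.* In the comparison within the DNA arm, relatives can fall into different genotype groups, so the unadjusted test need not be anti-conservative. No calculation here supports extending the point to Hypotheses II and III.

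**Conclusion.** The concern holds at moderate to low severity. The protocol treats an imprecise estimate as an established zero, and on that ground makes an analysis primary that does not match the family randomisation. If the true ICC is 0.3 to 0.38, the design effect is 1.07 to 1.09 and power is about 78%, some three percentage points below its value at ICC 0. The primary interval and p-value are then slightly too favourable, by the amounts tabulated above. If the ICC really is zero, nothing changes.

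These figures rest on pair counts derived from the protocol's averages, on all multi-member families being pairs, on the reported zero being the estimate itself and not a negative value set to zero (which would lower the upper limit), and on the final family sizes resembling those at the interim look.

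**What to change.** 1. Make the family-adjusted analysis primary for the between-arm comparisons: the Donner-adjusted chi-squared test already cited, or a GEE with family-robust standard errors, with a matching confidence interval. Report the unadjusted test as supportive.
2. Reword the sensitivity statement so that it does not presume that clustering makes no difference.
3. Replace the claim that power is unaffected with a power of about 78% to 81% over ICC 0 to 0.38. Report the interim ICC with its interval and the number of multi-member families.

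The cost is a change of wording and the exchange of two analyses, one of which is already planned. The stated power becomes slightly less favourable. No extra participants or data are needed.

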#### (b) Hypotheses II and III

Amongst the 200 followed-up in the DNA analysis arm it is expected that 44 will be heterozygous for NOD2, six homozygous, and 150 mutation negative. The following sets of secondary comparisons will be made to test Hypotheses II and III:

II(a) Within DNA arm: 0 mutations vs. 1 or 2 mutations

II(b) Between non-DNA arm and a subgroup of DNA arm (1 or 2 mutations)

III Between non-DNA arm and a subgroup of DNA arm (0 mutations)

The odds ratios that can be detected with 80% power with the above group sizes at the 5% level of significance are as follows:

II(a): An average odds ratio of 2.5 within DNA arm both in the absence of any difference between the randomised groups (29% in 0 mutations group versus 52% in 1 or 2 mutations group; group average 35%; detectable OR = 2.55) and in the presence of a difference between the randomised groups (43% in 0 mutations group versus 65% in 1 or 2 mutations group; group average 49%; detectable OR = 2.45).

II(b): There is 80% power to detect an odds ratio of 2.5 between the non-DNA arm and those with 1 or 2 mutations in the DNA arm (35% in the non-DNA arm versus 57% in the 1 or 2 mutations group of the DNA arm; detectable OR = 2.45).

III: There is 80% power to detect an odds ratio of 0.5 between the non-DNA arm and those with 0 mutations in the DNA arm (35% in the non-DNA arm versus 21% in the 1 or 2 mutations group of the DNA arm; detectable OR = 0.50).

### Randomisation

#### (a) Procedure

The research counsellor (KCL) will enroll each participant into the trial and the trial coordination team (KCL) will send each participant's data for randomisation to the statistical team (Cambridge), and receive back the allocated group.

#### (b) Method

Each participant will be cluster randomised by family to one of the two arms, with allocation on a 1:1 basis. The allocation method will be blocked randomisation with the randomisation sequence prepared by the trial statistician.

#### (c) Concealment

The randomisation sequence will be concealed from the trial co-ordination team and research counsellor and the statistical team will only be given study identification data necessary for randomisation. Participant date of birth will be required at study closure to confirm agreement between the generated sequence and that used in the trial. After assignment of a participant, neither the research counsellor nor the participant will be blind to the participant's study arm.

### Research governance

COREC approval has been given (REC: Hertfordshire 1: 06/Q0201/19, 26^th ^June, 2006).

R&D approval has been obtained from the hospitals (42 NHS Trusts across the UK) through which the probands will be contacted, and from the South London and Maudsley Trust, the employer of the research counsellors.

### Fidelity checks

All telephone calls will be tape-recorded. A sub-sample of these recordings will be randomly selected and transcribed to assess fidelity to the clinical protocol. The tapes will be stored in a locked cabinet and a sample analyzed on a regular basis.

### Adverse events monitoring

All comments made by participants and health care professionals will be logged in the Trial Log File. They will be given an individual number and also logged on a computer database. Any follow-up or further action needed will also be logged. No personal information will be included unless absolutely necessary. The file will be stored in a locked office.

Any incident considered serious is to be entered in the Adverse Incident Log. This is a hardbound book that will also be stored in a locked office. A judgement about the incident's severity will be made between the Principal Investigator and the research team. Any incident included here will have a sheet in the Trial Log File and will also be logged on a computer database. Any follow-up or further action will be included in the book, alongside details regarding how the incident was resolved. No personal information will be included unless absolutely necessary.

An example of how adverse events monitoring could take place is as follows:

If a participant becomes anxious after learning of their risk of developing CD, the PI and research team will be informed and the incident logged. An appropriate procedure will then be initiated. Depending upon the nature of the anxiety, the participant will be encouraged to visit their GP or will be offered an appointment with of the trial's gastroenterology consultants. The outcome of this contact will be monitored and logged and the participant's GP informed, if consent is given for this.

Any incident judged to be severe by the Principal Investigator and the research team will be reported to the Data Monitoring and Ethics Committee within 24 hours.

### Statistical analysis

The analysis of the primary outcome, the proportion of participants reporting having made one or more quit attempts of 24 hours or more in the preceding six months, and the secondary cessation outcomes will be compared between arms by estimating a difference in proportions between arms together with a 95% confidence interval, and the p-value from the associated chi-squared test. The odds ratio and 95% confidence interval will also be reported. Analyses will be on an intention to treat basis with the common assumption for secondary cessation outcomes that all participants are classified as smokers except for those biochemically verified as non-smokers. However, for the primary outcome, those missing this outcome will primarily be treated as missing from the analysis. Missing status will be compared between groups, and the primary difference in proportions will be re-assessed assuming that missing data is imputed as no quit attempt. All tests will be two-sided and assessed at the 5% significance level. Sensitivity analyses will be performed to confirm that clustering makes negligible difference to results and no difference to conclusions or interpretations, using Donner's Method [27]. Hypotheses II and III will be assessed by comparing the primary outcome between mutation status subgroups of the DNA arm with each other and with the control arm. To strengthen the interpretation of these non-randomised comparisons, sensitivity analysis will be undertaken to vary the degree to which mutation status may predict outcome, detailed as part of the statistical analysis plan to be prepared prior to analysis.

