### Procedure

#### Participant recruitment

First degree relatives of people affected by Crohn's disease will be identified via three routes:

i. Probands receiving care through hospital services. Proband addresses will be obtained by gaining accesses to CD proband databases at participating hospitals, following the approval of the local hospital Trust Research and Development department. Probands may be given study invitation packs or telephoned by members of the clinical team.

ii. Probands who are members of the National Association for Colitis and Crohn's Disease (NACC). All members who have CD will be posted an invitation pack.

iii. Advertising in the newsletters of NACC and the charity Ostomy Lifestyle.

Probands will be posted a study information booklet and consent form. They will be asked to inform any FDRs of theirs who smoke and who are unaffected by CD or ulcerative colitis about the study. They will be asked to indicate on the consent form their preferred method for the study team to contact their relatives, either requesting the study information from the research team in order to give this to their relatives themselves, or providing their relatives' contact details, for the research team to make the contact. This procedure was developed as part of a feasibility study for this trial [18].

Information booklets and consent forms will be distributed to identified FDRs. Eligible FDRs who have read and understood the study information booklet will sign and return the consent form to the research team at KCL. The research counsellor will then telephone the participant and obtain further verbal consent before entering them into the trial.

#### Telephone call 1

Information will be collected about the participant's family history of CD to contribute to the risk assessment, as well as demographic and smoking characteristics. The participant's date of birth will be noted for randomisation at a later date.

Participants will be randomised after Telephone call 1. Those randomised to the DNA arm will be asked to provide a saliva sample for a DNA test. Non-DNA arm participants will not undergo a DNA test and hence will not be asked to provide a saliva sample. The trial co-ordinator will then send the results booklet to the participant (see *Communication of risk assessment for Crohn's disease*).

#### Telephone call 2

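### The primary comparison is valid and meets its stated power, but fixing it as unadjusted forgoes some precision that baseline data collected before randomisation could supply

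*Protocol article*

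**What the plan says.** The Statistical analysis section compares the primary outcome (one or more quit attempts of at least 24 hours within six months) between arms by "estimating a difference in proportions between arms together with a 95% confidence interval, and the p-value from the associated chi-squared test". It adds that "The odds ratio and 95% confidence interval will also be reported". For the primary outcome the only further analyses are a comparison of missingness between groups, a re-analysis counting missing as no quit attempt, and a check on clustering by Donner's method. No baseline covariate appears in any of these. The section refers to a separate statistical analysis plan only for the sensitivity analysis of the mutation-status comparisons.

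The Procedure section (Telephone call 1) says that family history is collected, "as well as demographic and smoking characteristics", and that allocation takes place after this call. The Additional outcomes section says: "Questionnaires administered within telephone calls 1,3 and 4 will assess key variables derived from three psychological theories". Both sets of variables therefore have a measurement before randomisation.

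**The concern.** Smoking characteristics, and variables from theories of motivation and behaviour, are plausible predictors of whether a smoker tries to stop. When such predictors are measured before allocation, adjusting for them removes outcome variation that has nothing to do with the intervention. The treatment difference is then estimated more precisely from the same participants. An unadjusted chi-squared test leaves that variation in the standard error.

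At stake is a modest amount of power and confidence-interval width on the main hypothesis. Because the article states the primary test outright, this is a choice already made and not a detail left open.

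**Working it through.** **Inputs.** Rates: "would be 35% in the non-DNA arm, enabling detection of 49% or higher in the DNA testing intervention arm (OR = 1.75") (Sample size, Hypothesis I). 200 per arm followed up, 470 randomised, 85% follow-up, no design effect in the revised calculation (same section). "All tests will be two-sided and assessed at the 5% significance level" (Statistical analysis). Allocation 1:1 (Randomisation, Method). The Abstract says the design "provides 80% power to detect a difference in the primary outcome of 14% between randomised arms, at the 5% significance level".

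**Step 1: reproduce the stated design.** The mean proportion is (0.35 + 0.49)/2 = 0.42.
- Null SE = √(2 × 0.42 × 0.58/200) = 0.0494.
- Alternative SE = √[(0.35 × 0.65 + 0.49 × 0.51)/200] = 0.0489.
- Power = Φ[(0.14 − 1.96 × 0.0494)/0.0489] = 81.2%.
- Sample size for 80% power = 194 per arm (208 with continuity correction).
- Randomised = 400/0.85 = 471, against 470 stated.

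The plan's figures reproduce without adjustment. The two rates give an odds ratio of (0.49/0.51)/(0.35/0.65) = 1.78, where the article gives 1.75. At exactly 1.75 the DNA-arm rate is 48.5% and power is 78.5%, still close to 80%.

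**Step 2: effect of adjustment.** If baseline covariates explain a share R² of outcome variance, the variance of the difference in proportions is multiplied by about (1 − R²). The effective sample size is then 200/(1 − R²) per arm. R² is an assumption throughout.

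| Assumed R² | Effective n per arm | Power | 95% CI half-width (points) |
|---|---|---|---|
| 0 | 200 | 81.2% | 9.6 |
| 0.02 | 204 | 82.0% | 9.5 |
| 0.05 | 211 | 83% | 9.3 |
| 0.10 | 222 | 85.1% | 9.1 |
| 0.15 | 235 | 87.0% | 8.8 |
| 0.20 | 250 | 89.0% | 8.6 |

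**Step 3: check by simulation.** 6,000 trials per setting, 200 per arm, one normally distributed prognostic score. The chi-squared test was compared with the treatment test from a logistic model containing the score. The Monte Carlo error of each power is about 0.5 points.

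| R² (AUC of score) | Chi-squared | Adjusted |
|---|---|---|
| 0 (0.50) | 81.6% | 81.8% |
| about 0.02 (0.58) | 81.2% | 82.2% |
| about 0.05 (0.63) | 80.6% | 83.0% |
| about 0.10 (0.68) | 80.8% | 84.1% |
| about 0.17 (0.74) | 79.7% | 87.3% |

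The gains are about 1, 2.4, 3.3 and 7.6 points. The last is somewhat flattered, because the unadjusted result in that setting fell below 81.2% by chance. The standard deviation of the standardised risk difference, relative to the unadjusted one, was 0.0462/0.0485 = 0.95 at R² of about 0.10, which matches √(1 − 0.10) = 0.95. With a useless covariate nothing was lost.

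**The case against.** The strongest objection is that nothing here is wrong. A chi-squared comparison of two randomised arms is valid, it matches the sample-size calculation, and it delivers the power claimed. Chance imbalance is already allowed for in the confidence interval and the 5% level. The gain rests on an R² that the documents do not supply and may be small. The article does not say which theory-derived variables are taken at which call, and it does not name intention or motivation to stop as a call 1 measure. Changing a primary analysis after half the originally planned participants have entered an interim analysis also carries a risk to credibility.

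Most of this stands and limits the point to efficiency. It does not remove the point, since using baseline values already collected costs almost nothing, even when they turn out not to be prognostic.

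A reader might infer several stronger things that the documents do not support:
- **That the main hypothesis is underpowered or the estimate biased.** Step 1 shows the 80% target is met, and randomisation makes the unadjusted difference unbiased.
- **That chance imbalance is uncontrolled because no stratification is mentioned.** A condensed article's silence on stratification factors does not show there are none.
- **That Hypotheses II and III are confounded by ancestry with nothing to address it.** The DNA testing section does say "While the prevalence of NOD2 mutations is lower or zero in populations not of European ancestry". However, no section links ancestry to quitting or says that ethnic origin is recorded. The Statistical analysis section already calls these comparisons non-randomised and commits to a sensitivity analysis on how far mutation status may predict outcome, with details left to the analysis plan.
- **That the interim analysis revealed results by arm.** The article reports only completion, cluster size and intracluster correlation from it.

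**Conclusion.** The point holds as a low-cost improvement. The primary analysis is valid and adequately powered on its own assumptions, but it is fixed as unadjusted while baseline data suited to adjustment are collected before allocation. The likely gain is 1 to 4 percentage points of power for R² between 0.02 and 0.10, and about 6 points at 0.15. The confidence interval would be about 1% to 8% narrower over that range (1 − √(1 − R²)). These figures assume 35% versus 49%, 200 followed per arm and no intracluster correlation. The R² values are illustrative.

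The precision gain applies to the difference in proportions. An adjusted odds ratio is a different, conditional quantity. Its test gains power, but its standard error does not shrink.

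**What to change.** Before anyone who chooses the covariates sees outcomes by arm:

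1. Name a short set of variables actually collected at call 1, for example one measure of smoking intensity and one theory-derived variable.
2. Make the primary estimate a covariate-adjusted difference in proportions, obtained by standardisation from a logistic model, with its 95% confidence interval and test based on family-robust standard errors.
3. Keep the unadjusted difference and chi-squared test as supportive, and label the odds ratio as conditional or unadjusted.
4. State that the covariates were chosen without knowledge of outcome by arm, given the interim analysis of the first 266 participants.

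The cost is a few sentences in the analysis plan and one more model. If the set is limited to variables already recorded at call 1, no new data are needed. The main constraint is timing, because a covariate set chosen after outcomes by arm are known would do more harm to credibility than the precision is worth.
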